#### Retrospective pneumonia chart review

##### Chart review procedures

To provide additional baseline data on adult pneumonia admissions in the four districts, including inter-district variability in the incidence of clinical pneumonia prior to PCV13 introduction, we undertook a retrospective chart review of all adult pneumonia admissions to the adult hospitals in these districts from January 2015 to the start of prospective adult hospital-based surveillance in March 2019. Data extraction was undertaken by trained staff and included clinical data, demographic data, district and subdistrict (khoro) of residence, age, date of birth, length of hospital stay, outcome and severity markers. No urine, nasopharyngeal swabs or digital CXRs were available for this period.

Staff reviewed admission registers for potential pneumonia admissions and then reviewed the relevant medical records to confirm whether patients met predefined pneumonia case definitions. Overall respiratory admission numbers and pneumonia admission numbers were also collected. To ensure that no cases were missed during the retrospective review period, staff retrieved all medical records for review where any respiratory system disease diagnosis was recorded in the admission log records to confirm whether the patient had pneumonia which met the study case definition or not. In addition, all intensive care unit (ICU) admissions and deaths were reviewed to ensure that severe disease cases were not missed. The medical records were analysed for the same severity markers as those recorded prospectively. The definition of severe clinical pneumonia remained standard across the pre- and post-PCV period.

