### Study design

The surveillance programme includes both retrospective (Jan 2015 - Feb 2019) and prospective (March 2019–March 2022) data collection. The study has a number of different components, including prospective pneumonia hospital-based surveillance with a nested case-control study, retrospective pneumonia chart review, data collection regarding other clinically relevant interventions and trends in cardiovascular and renal disease admissions as “control” conditions, and enrolment of controls without evidence of respiratory disease for validation of the urine antigen test [4].

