#### Prospective adult pneumonia hospital-based surveillance

##### Recruitment procedures

Prospective adult pneumonia hospital-based surveillance started on 1 March 2019. Participants are adults 18 years and older who are admitted with pneumonia to one of the four participating district hospitals and enrolled in the surveillance system. Hospital staff actively identify and screen all new adult respiratory admissions daily (from admission and other wards) to assess suitability for the study. Details regarding all patients screened, their eligibility and whether they were enrolled or not, as well as reasons for exclusion are captured on a screening/ enrolment log. Study staff review all admissions on a weekly basis to ensure that no eligible patients were missed. Any missed patients will be enrolled at time of identification.

If patients meet the clinical pneumonia case definition and provide written consent to be included in the study, clinical information is collected using an adapted case report form with details regarding presentation (e.g. oxygen saturation on admission), clinical management (e.g. provision and duration of supplementary oxygen) and risk factors for carriage and disease. If patients are unable to give consent – e.g., because of mechanical ventilation, severe illness, or mental incapacity – permission is obtained for enrolment from the next of kin to prevent severe cases from been missed.

Recorded risk factors include previous admissions for pneumonia and other conditions, level of education, recent migration to Ulaanbaatar, household size, number of children in the household, PCV vaccination status of children in the household, dwelling type, history of working in a mine, tobacco smoking, alcohol use, type of heating (coal, briquettes, electric or central) and type of stove in the household, history of tuberculosis, self-reported and documented comorbidities and pregnancy. Details regarding underlying medical conditions, antibiotic use and severity markers, e.g. blood pressure, respiratory rate, and level of consciousness according to the AVPU (“alert, verbal, pain, unresponsive”) scale and Glasgow Coma Scale [34, 35] are collected during medical record review. Prospectively enrolled participants will have digital CXRs, nasopharyngeal swabs and urine collected.

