#### Nested case-control study

This substudy will only include adults residing in households with children eligible to receive PCV13. Vaccine eligibility will be based on the relevant district vaccine introduction timelines. We will confirm household level vaccination data, obtained by verbal report, using clinic or electronic immunisation records if available. Children eligible to receive PCV13, who are identified as unvaccinated, will be referred to their local health centre for catch-up according to local guidelines.

When we identify an adult, who is hospitalised for pneumonia and who has children of vaccine eligible age living in the household, we will seek to enrol the adult and their household in the case-control study. We then conduct three separate case-control analyses (defined below) with respect to having any child in the house who received one or more doses of PCV13 compared with households having all PCV13-unvaccinated children.

The case-control comparison will be done for three endpoint-based subgroups.
Among adults hospitalised with pneumonia and with a CXR consistent with CAP based on clinical assessment at time of hospitalisation, VT pneumococcal pneumonia (case) compared with NVT pneumococcal pneumonia (control) based on serotype-specific urine antigen assays.Among adults hospitalised with pneumonia and with a CXR obtained, those with findings meeting adapted World Health Organization (WHO) paediatric radiological criteria (case) compared with those who have any other radiologic finding (control). This analysis is based on the assumption that pneumococcal pneumonia is more likely to have WHO endpoint consolidation CXR findings than non-pneumococcal pneumonia.Among adults hospitalised with pneumonia and with pulse oximetry performed, those with hypoxia (case) compared with those without hypoxia (control). This analysis is based on the assumption that pneumococcal pneumonia is more likely to be hypoxic than non-pneumococcal pneumonia.

These analyses will be controlled for relevant confounders, such as age and housing type.

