##### Statistical analysis plan

The primary analysis endpoint will be the change in severe clinical pneumonia incidence rate ratios (IRR) comparing the pre- and post-vaccine periods over 87 months in all four districts (Songinokhairkhan and Sükhbaatar with 17 months pre-PCV and 70 months post-PCV; Bayanzürkh with 30 months pre-PCV and 57 months post-PCV; and Chingeltei with 38 months pre-PCV and 49 months post-PCV). Retrospective data from 2015 will be used to contribute to pre-vaccine case numbers for the primary outcome. See Fig. 1 showing the schematic study timelines.

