**Fig. 1 Fig1:**
[figure not shown]
Schematic diagram of study design and timelines

The outcome variable for this analysis will be monthly district-level counts of severe clinical pneumonia. The IRR will be estimated using a mixed effects Poisson loglinear regression model (or a negative binomial model if there is over-dispersion) fitted to monthly counts, with log-transformed population denominators included as an offset. The model will include a fixed effect for PCV13 (indicator variable for PCV13 introduction which will depend on the district as PCV13 introduction was staggered), a fixed effect for time (time since study commencement in months) to account for temporal trends, and a random effect for district. The PCV13 term will be exponentiated to obtain the incidence rate ratio for the vaccine effect. This model assumes that there is uniform vaccine impact across the districts. Sensitivity analyses will explore whether the vaccine impact differs across districts and will include seasonality and employ changes in vaccine coverage as opposed to fixed PCV13 effects. A subgroup analysis will explore rate changes in different age groups (18–25, 26–45, 46–65 and > 65 years). We will also do a sensitivity analysis with a 1 year “lag period” for indirect PCV effect (as we don’t expect the indirect effect to be instantaneous).

For the secondary pneumonia endpoints, no pre-PCV13 radiological and urine data are available. Consequently, we will explore trends over time in the post-PCV13 introduction period, incorporating district and time since PCV13 introduction.

We will conduct a nested case-control analysis (“test-negative design” [46]) to measure the indirect PCV13 vaccine effectiveness among adults living with children eligible to be vaccinated with PCV13. The model will account for district and time since vaccine introduction. We will compare the odds of receiving PCV13 among household children between cases and controls, defined as: 1) adults with vaccine type (cases) versus non-vaccine type pneumonia (controls), 2) among adults who had a CXR, WHO defined radiological confirmed pneumonia (cases) versus no radiological pneumonia (controls) and 3) among adults who had pulse oximetry, hypoxic (cases) versus non-hypoxic (controls) pneumonia.

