### Study limitations

While our study includes four districts containing over 70% of Ulaanbaatar’s population, we did not include five of the city’s districts. Therefore, our findings may not be applicable to rural areas of the country. We only have 1 year of data pre-PCV13 introduction for all districts, however due to the phased introduction of the vaccine this period is extended in some districts. We have included both retrospective and prospective surveillance data which may potentially differ; however a standard clinical medical record was used in the district hospital sites over the entire period from 2015 with the same available clinical information for both periods, reducing the risk of discrepancies. We do not have pneumococcal carriage data for the retrospective period and have therefore chosen clinical endpoints as our primary study objective. The 2015/16 measles outbreak and annual variations in influenza and RSV cases may impact pneumonia outcomes; however, as we have administrative data available for both, we plan to incorporate this information into the descriptive interpretation of study results.

The adult surveillance programme in Mongolia will provide data to help guide paediatric and adult PCV immunisation policy in the country. It will contribute to the incomplete evidence available on the burden of pneumococcal pneumonia in adults in low resourced countries, particularly in the Asia-Pacific region. The study is one of the few active population-based pneumonia surveillance programmes evaluating the indirect impact of PCV in a resource-limited setting. With increasing introduction of PCV in low-resourced settings, the methods, experiences and lessons learned from our study may be used to guide the development of such systems in other countries.

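### The primary model has no term for the March 2019 change from chart review to prospective surveillance, so part of any step in case capture at that date would enter the PCV13 rate ratio

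*Protocol article*

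**What the plan says.** The Study design section splits the programme into "retrospective (Jan 2015 - Feb 2019) and prospective (March 2019–March 2022) data collection".

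The Statistical analysis plan section counts 87 months and gives each district's split, for example "Songinokhairkhan and Sükhbaatar with 17 months pre-PCV and 70 months post-PCV". Below Fig. 1 it sets out the model for monthly district counts of severe clinical pneumonia: "The model will include a fixed effect for PCV13 (indicator variable for PCV13 introduction which will depend on the district as PCV13 introduction was staggered"), then "a fixed effect for time (time since study commencement in months) to account for temporal trends, and a random effect for district", with a population offset. The sensitivity analyses named in the article cover district differences, seasonality, vaccine coverage, a 1-year lag and admissions for control conditions. None concerns the change of data source.

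On comparability, Chart review procedures says "The medical records were analysed for the same severity markers as those recorded prospectively" and that the definition of severe disease did not change. Study limitations says "We have included both retrospective and prospective surveillance data which may potentially differ", and answers that the hospitals used one standard medical record, holding the same clinical information, from 2015 onward.

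**The concern.** Every pre-PCV13 month is retrospective, and every prospective month is post-PCV13. A change in how completely severe cases are counted from March 2019 is therefore partly aligned with exposure, and the model has nothing else at that date to absorb it.

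The documents show three changes in capture at the switch:

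- **Consent.** Prospective enrolment needs consent from the patient or next of kin (Recruitment procedures; Informed consent). Chart review describes no such step. If the prospective counts are counts of enrolled cases, refusals lower them.
- **Exclusions.** The prospective criteria exclude people without 3 months' residence and readmissions within 14 days. The retrospective criteria list neither.
- **Oximetry.** Prospective patients have a study form with "details regarding presentation (e.g. oxygen saturation on admission"). Earlier values depend on the chart.

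The first two would lower prospective counts and the third would raise them, so the net direction is unknown. What is at stake is a modest bias in the primary rate ratio.

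**Working it through.** **Inputs.** January 2015 is month 1, so March 2019 is month 51 (4 × 12 + 3) and March 2022 is month 87. That gives 50 retrospective and 37 prospective months. PCV13 is on from month 18 in two districts, from month 31 in Bayanzürkh and from month 39 in Chingeltei. The Sample size estimation section gives 13,271 person-years per district-month, rates of 9.8 and 7.8 per 10,000, an intra-district correlation of 0.2 and alpha 0.05 (taken as two-sided).

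**The plan's own figure.** The standard stepped-wedge (Hussey-Hughes) variance is

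I·σ²(σ² + Tτ²) / [(IU − W)σ² + (U² + ITU − TW − IV)τ²], with I = 4 and T = 87.

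- U = 70 + 70 + 57 + 49 = 246
- V = 70² + 70² + 57² + 49² = 15,450
- W = 13 × 2² + 8 × 3² + 49 × 4² = 908
- At the mean rate of 8.8 per 10,000: σ² = 0.8 × 0.00088 / 13,271 = 5.3 × 10⁻⁸ and τ² = 0.2 × 0.00088 = 1.76 × 10⁻⁴

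The σ² terms in the brackets are negligible. The variance is about 4 × 87 × 5.3 × 10⁻⁸ / 5,328 = 3.5 × 10⁻⁹, so the SE is 5.9 × 10⁻⁵. Then z = 0.0002 / SE = 3.40, and power = Φ(3.40 − 1.96) = 92.5%, against the stated 92%. This formula gives every month its own effect. The analysis model as worded does not.

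**Leakage.** Expected counts (13,271 × 9.8 / 10,000 = 13.0 per district-month) were multiplied by an assumed factor from month 51 in all districts. The stated Poisson model was then fitted with linear month, and with fixed district effects in place of the random effect. The true rate ratio is 1.00.

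| Assumed step | Fitted PCV13 IRR | ln IRR / ln step | Rejection at nominal 5% |
|---|---|---|---|
| × 0.8 | 1.061 | 0.059 / −0.223 = −0.26 | 19% |
| × 0.9 | 1.027 | 0.027 / −0.105 = −0.25 | 8% |
| × 1.1 | 0.978 | −0.022 / 0.095 = −0.23 | 7% |
| × 1.2 | 0.961 | −0.040 / 0.182 = −0.22 | 12% |

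With a true ratio of 0.796, a step of × 1.2 gives 0.767 and × 0.8 gives 0.841. In the 1-year-lag analysis the sign reverses: under no effect, × 1.2 gives 1.033 and × 0.8 gives 0.969. With 87 separate month effects the leakage is zero. The rejection rates rest on the protocol's person-years and assume no over-dispersion.

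**With an indicator for months 51 to 87.** The fitted ratio returns to 1.000 or 0.796 for every step from × 0.7 to × 1.5. The term is identifiable because each district has retrospective months after introduction: 50 − 17 = 33, 50 − 30 = 20 and 50 − 38 = 12. The SE of the log ratio goes from 0.0566 to 0.0585 at a ratio of 0.796 (up 3.4%) and rises by about 4% under no effect. Power in this linear-time model goes from 98.1% to 97.4%.

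**What else loads on the indicator.** With no capture change at all, its coefficient is 0.94 if a true effect of 0.80 starts 12 months late, 0.96 if that effect builds over 24 months, and 0.95 under no vaccine effect with an assumed 30% fall from February 2020. Adding it moved the PCV13 ratio little in these cases (0.961 to 0.947, 0.940 to 0.930 and 1.166 to 1.150).

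**The case against.** A reader might infer that severity signs came from charts before March 2019 and from a study form afterwards. The documents do not support that. Recruitment procedures says blood pressure, respiratory rate and consciousness are taken from the medical record in the prospective period too. The recording concern is therefore mainly oximetry, one sign of four. ICU admission, pressor support in ICU and death also count as severe whatever signs are recorded, and all ICU admissions and deaths were reviewed retrospectively.

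A reader might also take the case-control wording, "Among adults hospitalised with pneumonia and with pulse oximetry performed", as evidence of poorer oximetry before 2019. That substudy belongs to prospective surveillance and says nothing about the earlier years.

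The retrospective search was thorough: every record with a respiratory diagnosis was retrieved. Its Number of subjects section says cases met the study eligibility criteria, so the two exclusions may in fact have been applied. No passage shows that completeness changed. The separate analysis plan, not shown here, is said to cover changes to model assumptions for sensitivity analyses, so the absence of one from the article is not itself an error.

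All of this stands, and it limits the point. It does not remove it. The article fixes the primary model, concedes that the sources may differ, and offers a common record as reassurance without testing it. The cardiovascular and renal counts track care-seeking and admission practice. They do not track consent, exclusions or recording of signs.

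**Conclusion.** The point holds as a minor weakness of the primary model. It is not shown that the rate ratio will be biased. If counted severe cases step by 10% to 20% in either direction in March 2019, a null ratio is reported as 0.96 to 1.06. This rests on three assumptions: the step sizes, which the documents do not give; the time term read as linear in months; and a step common to all four districts. If month were categorical, the problem would disappear.

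It would also be wrong to treat the indicator's coefficient as a measure of ascertainment change. Delayed vaccine effects, which the protocol expects, and COVID-19 disruption fall on it as well.

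**What to change.** 1. Add an indicator for March 2019 onward to the primary model or, at the least, name it as a sensitivity analysis of the primary rate ratio. State that its coefficient will not be interpreted as recording change alone.
2. In the 1-year-lag analysis, note that Chingeltei's lagged PCV13 term switches on in March 2019 (introduction in March 2018 plus 12 months), the same month as the indicator. That district then cannot help separate the two.
3. Apply the 3-month residence and 14-day readmission exclusions to both periods where the records allow, and say where they do not.
4. Tabulate completeness of the four severity signs by period.

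The cost is one model term, about 4% on the standard error, one table and a check of retrospective eligibility.

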##### Number of subjects

There were 2500–3200 annual adult admissions at all four district hospitals from 2015 to 2018 identified from admission books, with 1200–1600 total pneumonia cases per year who had medical records extracted. Between 850 and 1220 adult pneumonia cases per year met the study eligibility criteria and were enrolled retrospectively. An additional 400 cases were enrolled in January and February 2019.

##### Eligibility, inclusion and exclusion criteria

Medical records were reviewed for all adults admitted to one of the four participating district hospitals with pneumonia from January 2015 to the start of the prospective surveillance in March 2019. Those adults who met one of the surveillance case definitions and lived in one of the four participating districts were included.

#### Clinical information collected on other relevant interventions and control condition

Ongoing information is collected on any changes in clinical practice or policies affecting pneumonia admissions instituted over the study period. This includes changes in antibiotic policies, antibiotic prescription practices, annual influenza vaccination campaigns (number of vaccine doses dispensed and coverage by age group) and changes in admission criteria.

There was a large nationwide measles outbreak in Mongolia which began in March 2015 and had two waves, March to September 2015 [38] and October 2015 to June 2016 [39]. A total of 49,908 suspected cases were reported, and 33,947 cases were confirmed. During the first wave, 9671/14,010 (69%) cases occurred among adults ≥15 years and 11,346/19,937 (57%) in the second wave [39]. We will also need to account for the potential changes in hospital admissions due to the ongoing COVID-19 pandemic and related public health interventions from 2020. To account for changes in hospital admissions due to the ongoing COVID-19 pandemic, we are collecting data on lockdown and other public health restrictions, COVID vaccination rates and vaccination status for admitted pneumonia cases. In addition, all adult respiratory cases are tested for SARS-CoV-2 on admission to hospital using rapid antigen testing and confirmation by PCR. Only SARS-CoV-2 negative pneumonia cases are enrolled into the surveillance programme.

To ascertain whether health-seeking behaviour and admission practices may have changed between the retrospective and prospective periods, admissions for two “control” conditions, cardiovascular and renal disease, will be collected over the entire study period (2015–2022) at all four hospitals for all adult patients. Weekly (prospective) or monthly (retrospective) numbers will be collected by age group and diagnosis category (for cardiovascular disease: ischaemic heart disease, heart failure, hypertension, cardiomyopathy, heart valve disease, vasculitis and other cardiovascular disease; for renal disease: pyelonephritis, renal failure, cystitis, glomerulonephritis and other renal disease).

#### Control enrolment for serotype-specific urinary antigen detection (SSUAD) testing

##### Recruitment

To establish positivity cut-off limits for the SSUAD assay in the Mongolian population (see “urine processing” section for details), urine samples were collected from 400 adult controls in June and July 2019 (i.e. during summer months, to reduce the probability of enrolling patients with recent or current respiratory infections). Staff screened all new non-respiratory adult admissions in the medical and surgical wards on a daily basis to assess suitability as a control for the study. If patients met the control inclusion and exclusion criteria and they provided written consent to be included in the study, clinical information was collected by the doctor using a questionnaire adapted from the case questionnaire. The control questionnaire included basic demographics, medical history and medication information. Controls were required to sign an informed consent form before a urine sample was collected. Any controls that tested positive on BinaxNOW® urinary antigen test, were disenrolled as controls. None of the seven controls who tested positive reported a recent admission for pneumonia [40].

Details regarding all patients screened, their eligibility and whether they were enrolled or not, as well as reasons for exclusion were captured on a screening/enrolment log. An equal number of controls were enrolled from each of the four hospitals and based on determined targets over four age groups (18–25, 26–45, 46–65 and > 65 years).

